#### Blinding

Participants will not be blinded to the allocation because this is not practically or economically feasible. Moreover, given the nature of the intervention, no blinding is possible at the LTCF level or for the researchers, and only the statistician performing the analysis will be blinded; unblinding will occur only after the completion of the analysis.

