### Multidisciplinary medication management program in long-term care facility residents

The MMMP in LTCF residents is a structured operationalized clinical pathway for comprehensive medication review (CMR), deprescribing, and multidisciplinary case conferences (MCC) by a team that includes visiting physicians, pharmacists, and nurses in partnership with the participants. In South Korea’s LTCF, a physician is not a resident, but they work outside and regularly visit the LTCF to administer treatment. Therefore, LTCF residents receive treatment from these physicians (visiting physicians) or from external physicians who treated them before they entered the LTCF. The MMMP uses an underlying secure digital platform (pacen-mmmpin.com (PACEN (website.ne.kr)], which integrates evidence to support multiple tools to check whether it is PIMs or not and cumulative medication burdens. This platform integrates consultation elements and evidence support across providers in shared electronic records.

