### Design

This is a prospective, cluster randomized, controlled, and open-label study comparing two LTCF residents’ group care strategies: (1) the intervention group, receiving an MMMP including CMR, deprescribing, and MCC, and (2) the control group, receiving typical usual care. The open procedure is the only possible option because of the nature of the intervention, which requires healthcare workers and participants to not be blinded. The study protocol was designed according to the Consolidated Standard of Reporting Trials (CONSORT) Statement. The Standard Protocol Items: Recommendations for Interventional Trials (SPIRIT) checklist and figure (Fig. 1) were used to prepare the study protocol. A flowchart showing an overview of the study is presented in Fig. 2.

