#### Clinical evaluation indices

##### Primary endpoints

The primary endpoints are (1) ADEs, (2) the number of PIMs and PIM users, (3) the ratio of PIMs and PIM users, (4) the number and ratio of users of two or more central nervous system (CNS) drugs, (5) all-cause delirium, (6) emergency department visits, (7) admissions, and (8) falls at T1-T6.

An ADE is defined as a severe adverse event, i.e., emergency room visits, hospitalizations, falls, and deaths due to “possible” abnormalities according to the World Health Organization-Uppsala Monitoring Centre causality evaluation criteria [10], or adverse drug reactions (ADRs) due to the use of drugs to be wary of or high-risk drugs for older adults. Medication-related information will be recorded to identify and describe the processes of medication change during and after the intervention. Locally acting topical agents without substantial systemic absorption or effects are excluded from the study. Acute short-course medications, such as antibiotics, are also excluded from the counts. This will be ascertained by a pharmacist after medication reconciliation, using dispensing, EMR, and participant information.

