### Follow-up and data collection

The evaluation will be performed at six different time points: T1–T6. The study procedure and data collection are detailed in Fig. 1 and have been established as per the SPIRIT guidelines. A research assistant will collect data from the pharmacists in the intervention group. For the control group, they will visit the LTCF and obtain baseline data from the institutional documents or EMR about the participant’s characteristics, including age, sex, general condition (long-term care level, disability, behavioral status [whether bedridden], and bedsores, if any), medical history (comorbidity), family history, vital signs, and laboratory test results. In addition, medication history, medication reconciliation, and outcomes are recorded as part of the clinical intervention. Data for security outcomes (falls, hospitalization, emergency department visits, and death) will be collected from the records or EMR directly from participating LTCFs. In the case of hospitalization or death of a participant during the follow-up period, no questionnaire for subsequent outcomes will be filled.

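### The Blinding section rules out blinding for all researchers, on reasons that cover only residents and those delivering care, so whoever grades adverse drug event causality knows the arm

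*Protocol article*

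**What the plan says.** On who is blinded, the Blinding section is categorical: "no blinding is possible at the LTCF level or for the researchers, and only the statistician performing the analysis will be blinded".

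The reasons appear in two other places. The Design section says: "The open procedure is the only possible option because of the nature of the intervention, which requires healthcare workers and participants to not be blinded". Under Randomization, the article adds that residents take part in the medication reconciliation, so the study has to be open.

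The Primary endpoints section begins: "The primary endpoints are (1) ADEs, (2) the number of PIMs and PIM users". It defines an ADE by attribution. Emergency visits, hospitalizations, falls and deaths count when they are "due to “possible” abnormalities according to the World Health Organization-Uppsala Monitoring Centre causality evaluation criteria". Adverse reactions to high-risk drugs, or to drugs calling for caution in older adults, also count. The section does not say who assigns the causality category. Its sentence on ascertainment by a pharmacist follows the rules for counting medications and may not extend to ADEs.

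The Discussion acknowledges the open label. It relies on the cluster design and on following a pre-determined method to limit bias, and on intention-to-treat to limit attrition bias.

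**The concern.** The intervention makes it impossible to blind residents, facility staff and those who review and change the drugs. It does not by itself make it impossible to blind a person who reads an event record afterwards and decides whether a drug was a possible cause. The Blinding section goes from the first to the second without a further reason.

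The programme reviews and withdraws drugs, and the ADE endpoint asks whether a drug caused the event. A grader who knows that a home ran the programme may be readier to acquit the drugs. One sensitised by the programme to drug harm may be readier to blame them. Either tendency moves the ADE comparison when there is no true effect. The bias is in the data before the blinded statistician receives them.

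**Working it through.** The plan gives no figure on this point, so the check is mainly a comparison of sections.

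**1. Scope of the reason against scope of the conclusion.** Design: healthcare workers and participants. Randomization: participants. Blinding: everyone at facility level and all researchers. The conclusion is wider than the reasons by one group, namely researchers who neither deliver nor receive the programme.

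**2. Is there a judgement to protect?** Yes. Both routes into the ADE definition require attributing harm to a drug. One of them is graded "according to the World Health Organization-Uppsala Monitoring Centre causality evaluation criteria".

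**3. Who makes it?** Not stated. The step is an inference: only the statistician is blinded, so any other person who assigns the category is not.

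**4. Do the stated safeguards reach it?**
- Cluster design: this limits contamination within a home, but knowing the home then reveals the arm.
- Pre-determined method: this standardises conduct but does not hide the arm.
- Intention-to-treat, later statistical adjustment and a blinded statistician: all act after the category is recorded.

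**5. Is masked grading possible?** The Follow-up and data collection section takes falls, hospitalizations, emergency visits and deaths from facility records or electronic medical records. There is therefore a written source from which an extract can be made.

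**6. Is this the same as unequal data sources?** No. That section also says "A research assistant will collect data from the pharmacists in the intervention group" and "For the control group, they will visit the LTCF and obtain baseline data from the institutional documents or EMR", the second sentence being about baseline data. That is a separate matter. Identical records graded with the arm known would still be open to this bias.

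**7. How an assumed grading difference would carry through (illustration, not an estimate).** The article gives no ADE rate, misattribution rate or intracluster correlation. Assume no true effect, a true ADE risk p of 10% to 30%, and a share s of true ADEs attributed in each arm.

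- Observed risks are p × s, so the apparent risk ratio is s(intervention)/s(control) whatever p is: 0.80/0.90 = 0.89 and 0.70/0.90 = 0.78.
- Effective sample size: 40.7% PIM (potentially inappropriate medication) users and an odds ratio of 0.41 give odds 0.407/0.593 × 0.41 = 0.281, or 22.0%. At two-sided 5% and 95% power this needs 157 per arm without clustering. The stated 715 per arm implies a design effect of 715/157 = 4.55. Applying that to ADEs is a further assumption, and it makes the effective size 157 per arm.
- Chance of a false significant benefit = Φ[(d − 1.96 × SE₀)/SE₁], where d is the risk difference and SE₀ and SE₁ are the pooled and unpooled standard errors. For p = 30% and 90% against 70%, the observed risks are 0.27 and 0.21. The odds ratio is (0.21/0.79)/(0.27/0.73) = 0.72. SE₀ = √(2 × 0.24 × 0.76/157) = 0.0482 and SE₁ = √((0.1971 + 0.1659)/157) = 0.0481. Then (0.06 − 0.0945)/0.0481 = −0.72, and Φ = 24%.

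| True ADE risk | Attributed, control / intervention | Apparent odds ratio | Chance of false benefit (nominal 2.5%) |
|---|---|---|---|
| 10% | 90% / 80% | 0.88 | 5% |
| 20% | 90% / 80% | 0.87 | 7% |
| 30% | 90% / 80% | 0.85 | 9% |
| 10% | 90% / 70% | 0.76 | 10% |
| 20% | 90% / 70% | 0.74 | 16% |
| 30% | 90% / 70% | 0.72 | 24% |

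Swapping the arms gives the same chances of a false harm. The table restates what is fed into it. It shows sensitivity, not that such a difference will occur.

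**The case against.** **The grader is not named.** A condensed article may leave adjudication to a fuller protocol, and the supplementary texts are not shown. A reader might infer that the article says causality is graded by someone who knows the arm. It does not say so, and the absence of a named grader is no fault in itself. What stands is the positive statement that only the statistician is blinded. Masked grading described elsewhere would contradict it.

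**Causality cannot be judged without the drug history.** Calling a fall less drug-related after the suspect drug was stopped can be a correct grading. This is right, and it limits the remedy: the history must stay in view, and drug changes will sometimes reveal the arm. Partial masking still removes the home, the arm label and the programme's own notes.

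**Medication endpoints.** A reader might extend the point with equal force to PIM status. The documents do not support that. The platform "integrates evidence to support multiple tools to check whether it is PIMs or not and cumulative medication burdens", and the Discussion calls the tools explicit, which leaves less room for judgement. No section says that the classification is made at the home.

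**The rest of the primary set.** Emergency visits, admissions and falls are also primary endpoints, counted without attribution, and the sample size rests on PIM users. ADEs are listed first, but nothing ranks them first. A shift in attribution alone would appear as an ADE result without support from the event counts. This stands and narrows the consequence.

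**Data access.** The Data protection section lets a facility's team see only its own residents. That governs facility teams on the platform. It does not stop the research team from supplying de-identified extracts to its own members.

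**Conclusion.** The point holds in a limited form. The Blinding section declares blinding of researchers impossible on grounds that do not cover a grader working from records. Under that statement, whoever assigns ADE causality knows the arm, and nothing in the Discussion removes the resulting detection bias. This rests on one inference, from the Blinding section to an unnamed grader.

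The direction and size of the bias are unknown. A reader might conclude that it favours the programme, or take the odds ratios of 0.72 to 0.88 as an estimate. Neither is supported, because every rate behind them is assumed. The reach is mainly the ADE endpoint, so this should be corrected but does not undermine the trial as a whole.

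**What to change.** In the Blinding section, limit the statement that blinding is impossible to residents, facility staff and those who deliver the programme. The Design section needs no change, because its reason is already limited to healthcare workers and participants.

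Add that ADE causality will be graded by existing research-team physicians or pharmacists who are not involved in the home concerned. They would work from de-identified extracts supplied by the research team, by the same rules in both arms. Home, arm, medication-review notes and case-conference notes are removed, and the drug history is kept.

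Optional and secondary: derive PIM status, use of two or more central nervous system drugs, and polypharmacy by one program from the recorded drug lists in both arms.

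The cost is some redaction work and a reallocation of cases among graders. Someone has to grade each ADE anyway, so no extra reader and no procedure for residents is added. Two limits remain. Masking will be partial, for the reason given above. It also cannot correct differences in what homes notice and record, since ADE monitoring by nurses is itself a step of the programme.

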### Experimental and control interventions

Each participant included in the study will be randomized into one of the following two groups:

Control group

The control group will receive the typical clinical care, as routinely provided in the LTCFs where the study will take place. The only restriction applied would be that no other planned CMR, deprescribing, or MCC will be performed in the LTCF setting during this phase.

Intervention group

We developed an MMMP for LTCF residents as a multifaceted intervention that integrates available evidence tools and a team approach within a clinical pathway where decision-making is led by considering participants’ priorities.

The research team including physicians, pharmacists, and nurses will be informed of the approach and program development so the intervention is as “fit for purpose” and as feasible as possible [9]. To foster fidelity, participating visiting physicians, pharmacists, and nurses in LTCF will receive an in-person training session for the program and the entire intervention, as well as a demonstrative manual [9].

This program will be operationalized as a structured clinical pathway in an electronic web-based platform, called “MMMP in LTCF” (pacen-mmmpin.com [PACEN; website.ne.kr]). It serves as a shared record for all visiting physicians, pharmacists, and other relevant workforces participating in the pathway for access and review. It is designed to be used in conjunction with and complement the EMR. This platform records and integrates five domains (Supplementary Text 1).

Operational steps (Fig. 3)STEP 1: Explanation of the study and obtaining informed consentSTEP 2: Recruitment and registration of participantsSTEP 3: Collection of participant’s informationSTEP 4: Listing medications taken by the participantSTEP 5: CMR and counseling by pharmacistsSTEP 6: Visiting physicians’ referral for medication reconciliationSTEP 7: Medication reconciliation after the prescribing physician confirms the CMR results.STEP 8: Conducting MCC through the cooperation of multidisciplinary teams (visiting physicians, pharmacists, nurses, and NH workers)STEP 9: Sharing CMR results, deprescribing, and participant managementSTEP 10: Nursing care and monitoring of ADEs by nursesSTEP 11: Medication management education for the multidisciplinary teams in the LTCF.

**Fig. 3 Fig3:**
[figure not shown]
Eleven-operational step-containing multidisciplinary medication management program. ADE, adverse drug event; LTCF, long-term care facility

A detailed description of the operational steps is provided in Supplementary Text 2.

### Endpoints/evaluation criteria

The evaluation indices comprise clinical and process evaluation indices, and the clinical evaluation indices comprise primary and secondary outcomes. Primary and secondary outcomes will be measured at baseline (T1), at the end of the intervention (T2), as well as at 3 (T3), 6 (T4), 9 (T5), and 12 months (T6) after the end of the intervention for effectiveness analysis. Figure 1 shows a detailed schedule of data collection.

#### Clinical evaluation indices

##### Primary endpoints

The primary endpoints are (1) ADEs, (2) the number of PIMs and PIM users, (3) the ratio of PIMs and PIM users, (4) the number and ratio of users of two or more central nervous system (CNS) drugs, (5) all-cause delirium, (6) emergency department visits, (7) admissions, and (8) falls at T1-T6.

An ADE is defined as a severe adverse event, i.e., emergency room visits, hospitalizations, falls, and deaths due to “possible” abnormalities according to the World Health Organization-Uppsala Monitoring Centre causality evaluation criteria [10], or adverse drug reactions (ADRs) due to the use of drugs to be wary of or high-risk drugs for older adults. Medication-related information will be recorded to identify and describe the processes of medication change during and after the intervention. Locally acting topical agents without substantial systemic absorption or effects are excluded from the study. Acute short-course medications, such as antibiotics, are also excluded from the counts. This will be ascertained by a pharmacist after medication reconciliation, using dispensing, EMR, and participant information.

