### Statistical considerations

#### Sample size, power, and statistical methods

Sample size calculations for the cluster RCT were performed by the team biostatistician. The required number of participants was calculated from the primary endpoint, that is, the number of PIM users. Based on recent literature, PIM users in LTCF comprised 40.7% [6], and the expected effect difference through literature review was an odds ratio of 0.41 [11]. Calculating the sample size using Sample Size Calculator V2.0 (Health Services Research Unit, University of Aberdeen) with a two-sided significance level of 5% and 95% power, 1,430 participants are needed (715 in each group). A total of 1,672 participants (836 in each group) should be included to prevent a dropout rate of 15% (discharge, hospitalization, death, etc.).

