#### Data analysis

The analysis will follow the intention-to-treat approach.

All analyses will be performed using SAS software (version 9.4; Cary, NC, USA). Statistical significance is defined as *p* < 0.05. This methodology follows the Consolidated Standards of Reporting Trials Statement (http://www.consort-statement.org/consort-statement) [12]. Interim analysis is planned at midpoint after the start of participants’ enrollment and when issues arise during the study, and missing data will not be replaced. If issues arise during the study, the study design will be modified.

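### Eight endpoints are listed as primary with no lead endpoint or visit, but the trial is sized on one, PIM users, under a single p < 0.05 threshold

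*Protocol article*

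**What the plan says.** Three sections of the protocol article bear on this.

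- **Primary endpoints.** The list opens "The primary endpoints are (1) ADEs, (2) the number of PIMs and PIM users, (3) the ratio of PIMs and PIM users", continues with users of two or more CNS drugs as item 4, and closes "5) all-cause delirium, (6) emergency department visits, (7) admissions, and (8) falls at T1-T6". That is eight numbered items over six time points. The abstract also gives a plural list of primary endpoints, unnumbered. Neither place names a lead endpoint or a primary visit. The Endpoints/evaluation criteria section makes clear that the first time point precedes treatment: "Primary and secondary outcomes will be measured at baseline (T1), at the end of the intervention (T2" and four later visits.
- **Sample size, power, and statistical methods.** Here there is one primary endpoint: "The required number of participants was calculated from the primary endpoint, that is, the number of PIM users". The inputs are "PIM users in LTCF comprised 40.7% [6" and "the expected effect difference through literature review was an odds ratio of 0.41 [11", and the result is that "with a two-sided significance level of 5% and 95% power, 1,430 participants are needed (715 in each group".
- **Data analysis.** One general rule is given: "Statistical significance is defined as *p* < 0.05".

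**The concern.** The article gives two accounts of what the trial is meant to confirm. Under one, any of eight outcomes at any of several visits is a primary result. Under the other, there is a single primary outcome, which carries the whole power calculation.

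With one threshold of 0.05 and no ordering in the text, a reader could accept a significant result on any listed endpoint as a positive trial. The false-positive risk would then exceed the nominal 5%. If instead the error were controlled by dividing alpha across all eight, the 95% power would no longer hold even for PIM users. The article gives no power for ADEs, delirium, emergency visits, admissions or falls. The trial is open-label and has an interim analysis planned, so a choice of endpoint or visit made later could not be shown from this article to have been prespecified.

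**Working it through.** **Inputs from the article.** Control proportion of PIM users 40.7%; odds ratio 0.41; two-sided alpha 5%; power 95%; 715 per group; 22 nursing homes (11 per arm at 1:1); 8 numbered primary endpoints; 5 post-baseline visits (T2-T6).

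**Assumptions.** The article states neither the ICC nor the correlations between endpoints and visits. Both are varied below.

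**1. The plan's own sample size.**
- Control odds = 0.407/0.593 = 0.6863. Multiplied by 0.41 this gives 0.2814, so the intervention proportion is 0.2814/1.2814 = 0.2196 and the difference is 0.1874.
- An individually randomised comparison at two-sided 5% and 95% power needs 157 per arm.
- 715/11 = 65 evaluable residents per cluster. With an assumed ICC of 0.05, the design effect is 1 + 64 × 0.05 = 4.2.
- 157 × 4.2 = 659, and 659/65 = 10.1, which rounds up to 11 clusters, or 715 per arm.

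The stated figure is therefore consistent with an ICC near 0.05, one endpoint and alpha 0.05. Because the ICC is assumed, this shows consistency and is not a full reproduction.

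**2. Chance of at least one false positive, eight tests at 0.05.**
- Independent: 1 − 0.95^8 = 33.7%.
- Simulated, assumed common correlation 0.3, 0.5, 0.7, 0.9: 29.9%, 25.0%, 19.0%, 12.0%.

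**3. The same if all five post-baseline visits are also tested separately (8 × 5 = 40 tests).**
- Independent: 1 − 0.95^40 = 87.1%.
- Simulated, common correlation 0.3, 0.5, 0.7, 0.9: 74.6%, 56.8%, 37.3%, 18.4%.
- Separate assumed correlations between endpoints and between visits: 0.4 and 0.7 give 63%; 0.6 and 0.8 give about 47%; 0.6 and 0.9 give 40%.

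**4. Power for PIM users if alpha is divided by eight (0.05/8 = 0.00625).** The standard error of the difference is √[DE × (0.407 × 0.593 + 0.2196 × 0.7804)/715]. The t columns use 20 df (22 clusters minus 2); the normal columns use the same unpooled variance.

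| Assumed ICC | DE | SE | Difference/SE | Power at 0.05, t | Power at 0.00625, t | Power at 0.00625, normal |
|---|---|---|---|---|---|---|
| 0.05 | 4.2 | 0.0492 | 3.81 | 95.1% | 76.2% | 85.8% |
| 0.057 | 4.648 | 0.0518 | 3.62 | 93.0% | 70.6% | 81% |

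A pooled-variance normal approximation at ICC 0.05 gives 84.5%. Across methods, the stated 95% falls to about 71-86%.

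**The case against.** Several counter-arguments have force.

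- **Sizing on one of several primaries is common.** PIM users is itself in the endpoint list, and the sample size section does not claim power for anything else. This stands, and it narrows the conflict: the difficulty is that one section speaks of the sole primary endpoint, another lists eight, and nothing says which is confirmatory.
- **A multiplicity method may sit in an analysis plan or full protocol that is not shown.** This also stands. The absence of such a method is not the point. The point is that what the article does state about primary status is inconsistent, and a further document would leave the article's two accounts in place.
- **The 0.05 sentence is generic.** It does not say endpoint by endpoint that each is judged at that level, so the inflation figures are conditional on any one endpoint being enough. If all eight had to succeed, type I error would not inflate. Power would suffer instead: 0.95^8 = 66% even if each endpoint had 95% power independently. No such rule is stated.
- **The outcomes overlap.** ADEs are defined partly through emergency visits, hospitalisations and falls, and the PIM count overlaps with PIM users. That lowers the inflation, but even at a common correlation of 0.9 it is 12% for eight tests.

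A reader might infer that a spurious primary result is more likely than not. The documents do not support that: it needs 40 separately tested comparisons and at most moderate correlation, and no section describes visit-by-visit testing. One repeated-measures test per endpoint fits the text equally well. A reader might also count about eleven measures by separating the bundled items. With fixed denominators, however, the number and the ratio of users are the same between-arm comparison, so that count is too high.

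**Conclusion.** The concern holds as an internal conflict. The article lists eight primary endpoints at T1-T6 with no lead endpoint or visit, sizes the trial on one, and applies one threshold of 0.05.

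If any of the eight counts as success, the false-positive chance is 34% under independence and about 19-30% at common correlations of 0.7-0.3. If visits are also tested separately, the range is about 18-87%; its width reflects unknown correlations and an unstated testing scheme, so it should not be reduced to a single figure. Power of 95% applies to PIM users at 0.05 only and drops to about 71-86% if alpha is split over eight, assuming an ICC of 0.05-0.057 and 11 clusters of 65 per arm.

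None of this shows that 715 per group is wrong for the one endpoint it was calculated on. Listing T1 among the endpoint visits is a smaller drafting error, since baseline cannot carry a treatment effect.

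**What to change.** Reconcile the abstract, the Endpoints/evaluation criteria and Primary endpoints sections, and the sample size section:

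1. Name the proportion of PIM users at one post-baseline visit as the single confirmatory primary endpoint, tested at two-sided 0.05. This follows the trial's own sample size basis. Which visit it should be is for the sponsor to decide and state.
2. Make the other listed endpoints, and the other visits, secondary. Use either a prespecified hierarchy or Holm control, or report estimates and confidence intervals only.
3. Remove T1 from the endpoint visits and use it as baseline.

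**Cost.** No extra participants or data are needed; alpha stays at 0.05 and 715 per group is unchanged. By contrast, keeping eight primaries under Bonferroni with 95% power for PIM users would take 232 × 4.2 = 974, or 15 clusters of 65 (975) per arm, at an assumed ICC of 0.05 and the normal approximation.

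The real downsides are two. The clinical events lose primary status, although the stated aim includes health outcomes and service use. And because recruitment began in April 2022 and an interim analysis is planned, this is a substantive protocol and registry amendment. It must be documented as made before any comparative data, interim data included, are seen.
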